## Abstract

**Background:**

Studies report rates of mild cognitive impairment (MCI) in spinal cord injury (SCI) range between 10 and 60%. This broad estimate of MCI in SCI is most likely a result of: (i) inconsistent operationalization of MCI; (ii) heterogeneity among individuals with SCI; (iii) failure to account for MCI subtypes, thereby adding to the heterogeneity of samples; and, (iv) poor control for traumatic brain injury (TBI) that obscures differentiation of MCI attributable to TBI versus other factors. There is a paucity of longitudinal studies following the course of MCI in SCI, and none that account for multiple predictors of MCI, including interactions among predictors.

**Methods:**

An inception cohort longitudinal study will assess approximately 100 individuals aged 17–80 years with acute SCI, with measures taken at three timepoints (baseline, 3 months post-baseline, and 12 months post-injury). Data relevant to medical care received within the first 24–48 h of presentation to the emergency department will be analysed, as will measures of cognition, injury characteristics, medical history, personal factors, psychological status, psychosocial functioning, and quality of life. Latent class mixture modelling will determine trajectories for the primary outcome of interest, cognitive functioning and its subtypes, and secondary outcomes of interest such as depression. Multiple regression analyses will identify predictors of MCI and its subtypes.

**Discussion:**

The prospective design will reveal change in cognitive functioning across time and unveil different outcome trajectories; thus addressing the lack of knowledge on trajectories of MCI and MCI subtypes in SCI. Through subtyping MCI, we hope to yield groups of cognitively impaired individuals with SCI that are potentially more homogenous and thereby stable and predictable. This is the first study to capture emergency department and acute care diagnostic evidence of mild TBI, which has been poorly controlled in previous studies. Our study will also be the first to distinguish the contribution of TBI from other factors to the development of MCI in individuals with SCI.

**Trial registration:**

The study was prospectively registered with the Australian and New Zealand Clinical Trial Registry (ACTRN12619001702101) on 3rd December 2019.

## Background

Spinal cord injury (SCI) occurs as the result of damage to the nervous system and spinal cord, associated with bruising or severing in traumatic injuries [1], or to degeneration of the spine, infections, vascular accidents, or cancerous tumours in non-traumatic injuries [2]. SCI is associated with a range of secondary health conditions, including; sleep disturbance [3, 4], psychological disorder [5], chronic pain [6], fatigue [7, 8], and autonomic nervous system dysfunction [9, 10].

Cognitive impairment can be a significant problem following SCI, with a recent systematic review indicating the occurrence of cognitive impairment among individuals with SCI is in the range of 10 and 60% [11]. In line with this, it has been proposed that individuals with SCI demonstrate an accelerated cognitive aging process [12, 13], to the extent that they may be 13 times more susceptible to cognitive impairment when compared to able-bodied individuals [14]. Studies in people with SCI have mostly investigated mild cognitive impairment (MCI), a form of impairment that is defined by subjective impairments that are objectively verified without serious impairments in functioning [15–19], raising questions regarding the clinical significance of cognitive impairment for SCI rehabilitation outcomes.

A number of issues have contributed to confusion regarding the definition and nature of cognitive impairment as it relates to SCI, with varying operationalisations of the construct making it difficult to confirm the severity and hence clinical relevance of cognitive impairment in SCI [11, 14]. These issues which limit understanding of the effects of MCI on outcomes following SCI are discussed below:

First, objective criteria for the confirmation of an impairment have varied greatly across SCI studies with respect to the stringency of criteria that have been applied and the types of tests utilized in the assessment of impairments [11]. It is therefore difficult to compare studies given the incorporation of different measures (e.g., scores on the Neuropsychiatry Unit Cognitive Assessment Tool [14] versus Rey Word Recognition Test [20] versus Symbol Digit Modalities Test [21]). Some studies have failed to pre-specify criteria for impairment altogether leading to reliance on significant between-group differences as proxies for impairment [12, 13]. Standard deviations (SD) from normal cognitive functioning that signify cognitive decline have ranged from 1 to 2 SD from the mean [14, 22]. Outside the SCI literature, a − 1.5 SD from normal in a single cognitive domain identifies the largest number of MCI diagnoses, compared to a − 2.0 SD in one or more cognitive domains which identifies the least [23].

Second, heterogeneity among participants has limited the predictive validity of the MCI diagnosis [11]. Individuals with SCI display different trajectories of MCI, varying from remission [21, 24], stabilization [25], to worsening [13], possibly as a result of distinct underlying ‘causes’ that can be identified as differentiable etiological subtypes [26, 27]. It has been suggested that the predictive validity of a MCI diagnosis improves by subtyping [28], but as far as known, there are no SCI studies that have applied subtyping to clarify such distinctions.

Third, most earlier studies have concentrated on traumatic brain injury (TBI) as the main cause of MCI, occurring before SCI, or at the time of SCI [22, 24, 29–37]. There are, however, many factors that contribute to the development of MCI after SCI [11]. These may include functional changes to the cardiovascular [38–40] and autonomic nervous system [41], psychological changes such as mood disturbances [42], medications [43–45], ageing [14, 46–48], sleep disorder [49, 50], fatigue [8], and social changes, such as the potential for decreased social participation [51, 52]. Some of these risks (e.g., depression, polypharmacy) are transient, while others (e.g., brain injury, cardiovascular dysfunction) contribute to degenerative or long-term courses of cognitive impairment. Therefore, it makes sense that MCI manifests differentially across individuals with SCI, who despite having SCI in common, often present with variable SCI-related complications indicative of different ‘risk profiles’. To study MCI in individuals with SCI it is important to apply risk-profiling to yield homogenous groups and to observe the time-course of risks independently and as a series of interactions. There are very few if any studies that fulfil this agenda.

As stated above, there are various factors associated with MCI after SCI. Autonomic nervous system disturbances and associated cardiovascular and cerebrovascular complications following SCI have been studied as risks for the development of cognitive impairment and poor SCI-related outcomes [38, 41, 53]. All individuals with SCI above the sixth thoracic segment (T6) suffer decentralised cardiovascular control, which has been found to predict cerebral hypoperfusion and consequently impaired cognitive performance [53]. Individuals with paraplegia can suffer persistent elevations in heart rate and related arterial stiffness, and this has been shown to predict suboptimal cognitive performance [54]. Measures of autonomic balance (measured by heart rate variability in this study), blood pressure, and heart rate, could be incorporated with other risk measures to generate risk profiles of the likelihood a person with SCI will develop vascular forms of MCI and guide monitoring and follow-up cognitive assessments.

TBI significantly increases an individual’s risk of MCI after SCI [11, 13, 18–26]. Mild and mild-complicated forms of TBI interfere less with cognition than do severe forms of TBI; however, mild-complicated and moderate TBI appear undifferentiable in terms of their influence on cognition [35, 55, 56]. Mild TBI is believed to account for up to 90% of TBI [57], with 10% being mild-complicated TBI [58] meaning there is evidence of intracranial lesions on structured neuroimaging techniques [59, 60]. Research concerning the relationship between SCI and TBI has failed to separate mild from other forms of TBI [32], possibly due to challenges in the acute identification of mild injuries (e.g., loss of consciousness assessed within 30 min of injury or amnesia assessed within 24 h post-injury). The difficulty of tracking people with mild TBI is exemplified by a study by Powell et al. [61] where the diagnosis of mild TBI in a non-SCI sample was missing in emergency department medical records in over 50% of individuals meeting Centers for Disease Control and Prevention criteria for mild TBI.

Research into medication-use in the rehabilitation of SCI and its relationship to the development of cognitive impairment is similarly inconclusive. Recently, Krebs et al. [43] found no relationship between antimuscarinic treatment of neurogenic lower urinary tract dysfunction and subsequent performance on neuropsychological testing after a treatment-period of 3 months. Two studies independently exploring the effects of anticholinergic burden and gabapentin on cognition found limited evidence of adverse reactions relating to the use of these medications in patients with SCI [44, 45]. These results are in contrast to a sizable body of evidence of negative associations between anticholinergic medication-use and cognitive impairment in able-bodied individuals [62–66] and individuals comprising other illness samples [67–71], and may relate to inadequate length of follow-up, insufficient statistical power to detect effects, and/or use of measures that lack sensitivity to detect cognitive decline.

Support for a relationship between MCI and depression in SCI has been found in three of six relevant studies [5, 8, 72]; however, lack of control for the effects of TBI makes it difficult to rule-out the contribution of TBI to this relationship. Major depressive disorder symptoms include difficulties with concentration and/or decision-making [73], so it is conceivable that depression contributes to MCI in some individuals with SCI, at least for the duration of a reactive depressive episode. Where depression is related to endogenous ‘causes’ as in the case of late-life depression or vascular depression [74], depression has predicted the conversion of MCI to Alzheimer’s disease in elderly able-bodied samples [42], suggesting that there is a strong link between cognitive decline and depression, where depression is biologically driven. Clearly, predictors such as depression possess heterogeneity that should be considered when exploring their relationship to the development of MCI and its course.

Finally, the impact of moderators of relationships between predictors of MCI and MCI need to be considered, and in this respect, attention must be given to age as a potential moderator of relationships. Four of five studies [14, 46–48] into the impact of age on risks associated with cognitive impairment following SCI have suggested that age compounds risks associated with cognitive impairment following SCI. This is significant given the mean age of new-onset SCI has increased since earlier studies into the relationship between cognitive impairment and SCI were conducted [75, 76].

In response to the aforementioned issues and with the intention of addressing the limitations of prior studies undertaken on the topic, we present a protocol for an inception cohort longitudinal study that will investigate factors contributing to cognitive impairment in individuals with SCI across a 12-month period with the incorporation of controls for the effects of TBI (i.e., non-TBI/cognitively impaired persons with SCI). We outline the study’s design and method below, including procedures for participant recruitment and allocation to groups, predictor and outcome measures, data collection, and statistical analyses.

## Methods

### Primary objectives

Determine the rate of MCI in adults with SCI, including MCI sub-types: single domain amnestic, multiple domain amnestic, single domain non-amnestic, and multiple domain non-amnestic;Identify predictors of MCI (e.g., mood disturbance, polypharmacy, presence of TBI) and moderators of relationships between predictors and MCI (e.g., education, estimated premorbid intelligence, practice effects);Investigate how predictors operate over time to influence manifestations and trajectories of MCI (e.g., how depression and/or polypharmacy affect MCI).

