### Variables

Table 1 shows predictors, primary and secondary outcome measures, and the assessment timepoints relating to each measure. As the table indicates, predictors are marked by a single asterisk whereas secondary outcomes are marked by a double asterisk. *Acute monitoring* (V0) refers to the time from first presentation to the emergency department to the time of consent; at which point, routinely collected data will be retrospectively retrieved from medical records. *At rehabilitation* (V1) may vary between five and 12 weeks following SCI as participants will vary with respect to the amount of time required spent in acute care prior to proceeding to rehabilitation. *Discharge* (V2) refers to a three- to four-month period following assessments completed at V1. The timepoint *in community* refers to 12-months after the date of the initial SCI.

**Table 1 Tab1:** Predictors, primary and secondary outcome measures, and assessment timepoints

Assessment time-points	Visit-type				
Study phase	Acute monitoring	At rehab		At discharge	In community
Visit number		(V0)	(V1)	(V2)	(V3)
Eligibility pre-screening (by treating Clinician)		✓			
Informed Consent			✓		

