#### Primary outcome measure

##### Neurocognitive testing

The Neuropsychiatry Unit Cognitive Assessment Tool (NUCOG) [80], a validated cognitive measure for SCI, will be used to screen cognitive functioning using age-adjusted normative scores provided in the administration and scoring manual to identify deviations from normal cognitive functioning. Means and SD for each of the five subscales comprising the NUCOG (attention, visuoconstructional, memory, executive, and language) permit analyses of patterns of performance across subscales. The tasks presented in each of the subscales are listed below:

Attention: Measures of orientation, forward and backward digit span, and the recitation of an overlearned sequence.

Visuoconstructional: Drawing reproduction, orobuccal and limb praxis, left-right orientation, spatially-directed attention, and calculation.

Memory: Verbal recall of words, spatial recall through the re-drawing of previously copied figures, autobiographical and other personal or historical details.

Executive function: Motor sequencing, categorical/semantic fluency, abstract thinking, and interference.

Language: Comprehension, repetition, naming, writing, reading, and word-finding.

Items requiring normal hand function (e.g., drawing reproduction) will be adapted as per previous studies where this has been shown to not alter the validity of NUCOG scores [81]. Where it is not possible to administer the NUCOG face-to-face (e.g., discharge to the community outside metropolitan areas within the state of NSW, Australia, or social distancing restrictions due to COVID-19), administration will occur via telehealth methods. Administration of the NUCOG via teleconferencing required further adjustments to the NUCOG assessment procedure to suit the telehealth environment. These procedural adjustments will be standardized, and validation will constitute part of this study.

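### Practice effects are named as a moderator in a primary objective, but the NUCOG schedule confounds them with time since injury, so a practice gain would look like remission of MCI

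*Protocol article*

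**What the plan says.** Under Primary objectives, the second objective is to identify predictors of MCI and "moderators of relationships between predictors and MCI (e.g., education, estimated premorbid intelligence, practice effects". The third asks how predictors act over time on the course of MCI.

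The NUCOG is the primary outcome and the only cognitive test listed in Table 1, ticked for V1, V2 and V3. The Variables section sets the timing:
- V1 "may vary between five and 12 weeks following SCI".
- V2 "refers to a three- to four-month period following assessments completed at V1".
- V3 "refers to 12-months after the date of the initial SCI".

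Under Neurocognitive testing, the NUCOG is scored "using age-adjusted normative scores provided in the administration and scoring manual to identify deviations from normal cognitive functioning". Under Participant allocation to groups, MCI requires scores more than 1 SD below normal on at least two tests within a domain, and both groups consist of people with SCI. Under Statistical methods, multiple regressions seek predictors of MCI at discharge and at 12 months, and latent class mixture models describe trajectories for the cognitive domains.

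**The concern.** A moderator needs variation between people, or within people over time, that is not already carried by another variable. Here everyone follows the same testing sequence. The article describes no group tested once, no repeat-tested reference group and no staggered first test. How often a person has seen the NUCOG is therefore almost the same thing as how long ago the injury was.

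The consequence goes beyond one item in an objective. The Background names remission, stabilization and worsening as the courses of MCI seen in SCI, and the study aims to describe such trajectories. If people score better on a second or third attempt because the tasks are familiar, a fixed cut-off will reclassify some of them from impaired to unimpaired. The result would read as recovery.

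**Working it through.** The plan gives no figure for practice, so there is none to reproduce. Its one computed figure, a sample size of at least 90, is not affected by this point.

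**Step 1: do the exposure windows overlap?** Inputs are the visit timings in the Variables section. One month is 365.25 / 7 / 12 = 4.35 weeks.
- First NUCOG (V1): 5 to 12 weeks after injury.
- Second NUCOG (V2): earliest 5 + 3 × 4.35 = 18.0 weeks; latest 12 + 4 × 4.35 = 29.4 weeks.
- Third NUCOG (V3): 12 × 4.35 = 52.2 weeks.

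The latest V1 (12 weeks) precedes the earliest V2 (18.0 weeks), and the latest V2 (29.4 weeks) precedes V3. For people who attend every visit, no two exposure counts are ever observed at the same time since injury.

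**Step 2: how strong is the confounding across visits?** I simulated 100 participants, with V1 uniform on 5 to 12 weeks, V2 at V1 plus a uniform 3 to 4 months, and V3 at 52.2 weeks. The uniform spread is an assumption. The variance inflation factor is VIF = 1 / (1 − R²), with R² from regressing exposure number on the time terms.

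| Assumed recovery curve | Correlation with exposure | VIF |
|---|---|---|
| Linear in time | 0.98 | about 26 |
| Linear in log time | 0.98 | about 22 |
| Quadratic in time | not applicable | about 54 |

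Separation is therefore weak, and it depends on the recovery curve chosen.

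**Step 3: the regressions at each visit.** Among participants with complete visits, exposure count is 2 for everyone at discharge and 3 for everyone at 12 months. A constant cannot be entered as a moderator.

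**Step 4: illustrated effect on the MCI rate.** Assume one normal score, no true change, and 40% below the cut-off at V1 (60 of 150 in the preliminary study cited under Study size). The cut-off is then z = −0.253. After a total practice gain of g SD, the rate is Φ(−0.253 − g).

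| Total gain g (assumed) | Share below cut-off |
|---|---|
| 0 | 40.0% |
| 0.1 SD | 36.2% |
| 0.2 SD | 32.5% |
| 0.4 SD | 25.7% |

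A gain of 0.2 SD at V2 followed by another 0.2 SD at V3 gives 32.5% and then 25.7%.

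**Step 5: illustrated effect on remission.** Remission is 1 − P(below at both visits) / 0.40, from a bivariate normal with retest correlation r. The value 0.5 matches the correlation assumed under Study size; 0.8 is a further assumption.

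| Gain at V2 | r = 0.5 | r = 0.8 |
|---|---|---|
| 0 | 40% | 25% |
| 0.2 SD | 49% | 34% |
| 0.4 SD | 58% | 45% |

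The first row is regression to the mean and arises without any practice. Practice is responsible only for the increase over that row: about 9 to 10 points at 0.2 SD and 17 to 20 points at 0.4 SD.

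**The case against.** Several points on the other side stand.

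- **Examples only.** The moderators are given as examples, so the second objective does not fail as a whole. Naming practice also shows that the authors are aware of it.
- **Not strictly inseparable.** The spread at V1, and people who miss V2 but attend V3, leave some information. It is slight, depends on the recovery model, and in the second case comes from a self-selected group.
- **Within-visit regressions.** A uniform gain is not a confounder between people who have had equal exposure at the same visit. The search for predictors at discharge and at 12 months is not biased by it in that sense.
- **The overall rate.** The first objective is not tied to V2 or V3 and can be met at V1, before any practice.
- **Trajectory classes.** The latent classes appear to be fitted to domain scores. A uniform gain tilts all curves together and does not by itself merge or reorder classes.
- **The illustration is simple.** It uses one score and one cut-off, whereas the plan requires two low tests within a domain. A move to telehealth at later visits, which the article allows, could add to a practice gain or mask it.

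A reader might also infer that the manual's norms make no correction for retesting. The article says only that they are age-adjusted and the manual is not shown, so that cannot be asserted.

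Nor do the documents support saying that premorbid intelligence, named in the same list, cannot be obtained. Table 1 has no such instrument, but its caption is "Predictors, primary and secondary outcome measures, and assessment timepoints", which does not promise moderators. Education has no row of its own either. The objective speaks of an estimate, which could be demographic, and the full protocol may name an instrument.

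None of this supplies variation in exposure at equal time since injury among people with complete visits, and a later analysis plan cannot create it.

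**Conclusion.** The point holds for practice effects. As scheduled, the study cannot estimate them as a moderator without assuming the shape of recovery, and even then only weakly (VIF about 22 to 54 under uniform visit times). With a fixed cut-off, any practice gain pushes the V2 and V3 MCI rates down and apparent remission up. That direction follows from the design, provided that the scores used carry no retest correction and that a change of mode does not offset the gain. The size is unknown, and the 40% to 32.5% shift is an illustration under an assumed 0.2 SD gain on a single score. What is affected is the interpretation of MCI rates after V1, of remission, and of the absolute direction of change in the trajectories. Class separation is less affected, and the V1 rate is not affected.

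**What to change.** 1. Remove practice effects from the moderators in the second primary objective, and state that practice and recovery are confounded in this design.
2. Report the V1 rate, at first exposure, as the MCI rate free of practice.
3. Add one sensitivity analysis: subtract a range of assumed practice gains from the NUCOG scores at V2 and V3, cumulative over the two visits, and then re-derive MCI status and remission. A range of 0.1 to 0.4 SD per repeat, for example, means 0.2 to 0.8 SD in total at V3. Describe remission as robust only where it survives the range.
4. Attach the same caveat to the absolute direction of change in the latent classes. Shifting the MCI cut-off would not address this, because it does not act on classes fitted to continuous scores.

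The cost is a change of wording and one extra analysis, with no new visit or test and no change to the sample size. The downside is that one stated moderator is lost and claims of cognitive improvement become more cautious.
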